### Group size/power analysis

Prior longitudinal studies stroke cohorts at Sahlgrenska University Hospital have had a dropout rate of 30%. With a power (1-β) at 0.8 and a significance level (α) at 0.05, we need a sample of 88 patients (two-sided test) to determine a medium effect of 6 points change (10%) on ARAT. Therefore, we aim to include 120 persons.

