## Methods/Design

A sample of 120 persons with a first occurrence of stroke will be included and followed longitudinally for one year after the stroke. The group will consist of consecutively included persons recruited from the stroke unit at Sahlgrenska University Hospital, Gothenburg, Sweden. The Stroke unit at Sahlgrenska University Hospital serves the larger Gothenburg urban area, thus all persons from this catchment area are randomly referred to the Sahlgrenska University Hospital. The project is approved by the Regional Ethical Review Board and the Helsinki declaration is followed. Written informed consent will be obtained from the participants or from their closest relative. The SALGOT study is registered on ClinicalTrials.gov (NCT01115348).

Inclusion criteria are:

• Diagnosed first ever clinical stroke, based on WHO criteria (ischemic infarct, haemorrhagic and subarachnoidal bleeding)

• Impaired upper extremity function. This is defined in two steps. On the first or second day after stroke onset the upper extremity function is assessed with Modified Motor Assessment Scale (M-MAS UAS-95) [33] (this is performed as standard clinical assessment by physiotherapists working at the stroke unit). All persons, who do not obtain the maximum score on the subtests of arm function, hand movements and fine motor function due to hemiparesis, will be informed about the study and retested at day three after stroke with Action Research Arm Test (ARAT) [34]. All persons who do not achieve the maximum score for ARAT (score 57) will be included.

• Admitted to the stroke unit within three days after stroke onset

• Living in the Gothenburg urban area (maximal 35 km from the Sahlgrenska University Hospital)

• Age 18 or older

Exclusion criteria are:

• Upper-extremity injury or condition prior to the stroke that limits the functional use of the affected arm and hand

• Severe multi-impairment or diminished physical condition before the stroke that will affect the arm function

• Life expectancy less than 12 months due to other illness (cardiac disease, malignancy) or severity of stroke injury

• Not Swedish speaking prior to the stroke incident

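### If the quoted 30% dropout recurs, 120 included leaves 84 evaluable, short of the 88 the protocol says it needs (a minor numerical inconsistency)

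*Protocol article*

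**What the plan says.** The section Group size/power analysis of the protocol article is a single short paragraph. It opens with the attrition experience at the hospital: "Prior longitudinal studies stroke cohorts at Sahlgrenska University Hospital have had a dropout rate of 30"%. It then sets the error rates, "With a power (1-β) at 0.8 and a significance level (α) at 0.05", and gives the requirement, "we need a sample of 88 patients (two-sided test"), which is meant "to determine a medium effect of 6 points change (10%) on ARAT". It closes with the target: "Therefore, we aim to include 120 persons".

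The target of 120 is repeated in the Abstract, in Methods/Design ("A sample of 120 persons with a first occurrence of stroke will be included and followed longitudinally for one year after the stroke") and in the Discussion. The article gives no other dropout rate and no other reason for including more than 88 people.

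**The concern.** The closing sentence presents 120 as following from what comes before it. The only stated inputs that could turn 88 into 120 are the 88 itself and the 30%. If 88 is the number that must remain and 30% is the expected loss, the target should leave at least 88 after that loss. It does not.

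This paragraph is the article's only statement of size and power, and the step from 88 to 120 can be checked from the printed figures alone. A reader who takes it at face value would believe that 80% power is kept after the attrition quoted two sentences earlier.

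**Working it through.** **Inputs, all from Group size/power analysis:** required number 88; dropout in earlier cohorts 30%; power 0.80; two-sided α 0.05; change to detect 6 ARAT points; target 120.

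**Attempt to reproduce 120 from 88 and 30%**
- Correct inflation, N/(1 − d): 88/0.70 = 125.7, so 126.
- Common incorrect inflation, N × (1 + d): 88 × 1.30 = 114.4, so 115.
- Neither gives 120.

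**What 120 delivers**
- Remaining after 30% dropout: 120 × 0.70 = 84, which is 88 − 84 = 4 short.
- Largest dropout at which 88 still remain: 1 − 88/120 = 26.7%, that is, 32 losses.
- In whole percentages: at 26%, 120 × 0.74 = 88.8, which is enough; at 27%, 120 × 0.73 = 87.6, which is not.

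**Power at 84.** The paragraph gives no standard deviation and names no test, so the 88 is taken as stated. The effect is scaled so that 88 gives exactly 80% power. No standard deviation is then needed, because the expected test statistic grows with the square root of the sample size.
- At 88: z(0.975) + z(0.80) = 1.960 + 0.842 = 2.802.
- At 84: 2.802 × √(84/88) = 2.802 × 0.977 = 2.737.
- Power: Φ(2.737 − 1.960) = Φ(0.777) = 0.781.
- Scaling a paired t-test in the same way also gives 78.1%.

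The loss is 80.0 − 78.1 = 1.9 percentage points.

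**Change detectable with 80% power at 84:** 6 × √(88/84) = 6 × 1.0235 = 6.14 points, against 6.0 at 88.

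**The case against.** The strongest reply is that the 30% is reported as past experience and not as a forecast for this cohort. The sponsor may expect better retention, and 120 is enough for any dropout up to 26.7%. This stands in part: the shortfall is conditional on 30% recurring. It does not remove the inconsistency, because the paragraph derives its target from that rate and the article gives no lower one. Nor can 120 be defended as rounding, since rounding from 125.7 to protect a minimum has to go up.

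A second reply is that the loss is trivial for a study whose main aim is to describe recovery. That is right about size. The study is non-interventional, and 0.14 of a point on a scale with a maximum of 57 changes nothing of substance. It bears on how serious the error is, not on whether there is one.

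Three stronger readings are tempting, and the article supports none of them.
- A reader might infer that the study is underpowered in any serious sense. About 78% in place of 80% is not that.
- A reader might infer that a 12-month comparison loses power. The paragraph does not say between which occasions the 6-point change is measured, and it does not tie the 30% to month 12. ARAT is scheduled at eight occasions, and a change over a shorter interval could lose fewer participants.
- A reader might infer that people who leave contribute nothing, or that a particular repeated-measures model has to be specified. The article does not say how partial follow-up will be analysed, and an article commonly leaves that to the full protocol or analysis plan. An analysis using partial follow-up could recover some of the loss, but power quoted on 84 completers would then no longer describe it.

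**Conclusion.** The point holds as a minor numerical error. On the paragraph's own figures, 120 included with 30% dropout does not leave 88; it leaves 84, and 126 would be needed. Under that dropout, power is about 78% and not 80%, and the change detectable with 80% power is about 6.1 points and not 6.0.

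The conclusion rests on two readings: that the quoted 30% is the planning assumption, which is the only one the paragraph offers, and that 88 is the number needed after losses. The count of 84 needs nothing more. The power figure also takes the 88 as giving exactly 80%, which cannot be checked without a standard deviation. The error does not threaten the validity of the study or its descriptive aim.

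**What to change.** Restate the figure in Group size/power analysis in one of two ways.
- Keep 30% and report what follows, for example: *120 included with 30% dropout leaves 84 evaluable, giving about 78% power for a 6-point change (80% for about 6.1 points).*
- Keep 88 and 80% power, and state, with a reason, that dropout of at most about 26% is expected in this cohort.

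Either is a change of wording only. The target of 120 stays as it is in the Abstract, Methods/Design and Discussion. The first option makes the stated power slightly less favourable; the second needs a justification for expecting better retention than the earlier cohorts had. Including 126 would also reconcile the figures, at the cost of six more participants, but a loss of this size does not require it.

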## Discussion

The SALGOT study is a longitudinal prospective study with a non-selected sample from Gothenburg urban area. A sample of 120 persons with first ever clinical stroke admitted to a stroke unit will be consecutively recruited from Sahlgrenska University Hospital. The study is non-interventional and the main goal is to describe the recovery of upper extremity function after first ever clinical stroke and to follow the improvements and consequences of stroke during the first year in these persons life. Measurements are performed both using traditional clinical assessments as well as computer based measurement systems that provide objective kinematic data. The person's perspective of recovery is captured both with stroke specific as well as generic self-perceived outcome measures.

In this study, the participants are assessed at eight occasions during the first year after stroke. This design gives an opportunity to study which persons will recover, when and in which areas the recovery occurs. From earlier studies it is known that the improvement of function is mostly gained during the first months after stroke. But the majority of these reports have been conducted on selected populations and in many studies the selection of outcome measures on motor function has not been sufficient. Additionally, new technologies obtaining objective kinematic measures on motor function and performance have been scarcely used in longitudinal studies.

The gained knowledge of recovery patterns is necessary both for the healthcare system and for the individual who has suffered a stroke. Since the rehabilitation resources are limited, there is a need to know the optimal time point for interventions and have guidelines for rehabilitation planning. The more detailed information about the recovery patterns of upper extremity is needed in order to offer individualized assessment and treatment, to inform the patient sufficiently about the recovery perspectives and to enhance the patient's motivation for the rehabilitation period.

## Abbreviations

ARAT: Action research Arm Test; BNIS: Barrow Neurological Institute Screen for Higher Cerebral Functions; EQ-5D: EuroQol Quality of Life Scale; FMA-UE: Fugl-Meyer Assessment for Upper Extremity; IPA-E: Impact on Participation and Autonomy; M-MAS UAS-95: Modified Motor Assessment Scale accordingly Uppsala Akademiska Sjukhus 95; NIHSS: National Institutes of Health Stroke Scale; SIS: Stroke Impact Scale; TOAST: Trail of Org 10172 in Acute Treatment; VR: Virtual reality; VE: Virtual Environment.
